#### Secondary outcome

Based on previous studies [19, 25, 26], secondary outcomes cover vital signs at T0, T1, and T2 to observe the impact of pain and intervention measures on the patient’s physiological index. The side effects, patient and therapist satisfaction (0: satisfied; 1: dissatisfied), the time for ROM ≥ 90° (according to our previous qualitative study, one of the substantial indicators of discharge from hospital for patients is range of motion ≥ 90°), and whether to add adjuvant analgesia will be obtained at T2 separately. Whether patients are willing to use the same gas again should also be recorded as an indicator and recorded.

### Sample size estimates

A prospective sample size estimate was conducted by a senior statistician using the GPower 3.1 procedure during the protocol-writing stage. The level of pain relief is regarded as the primary endpoint measure of this trial [27]. To achieve a statistical power of 80% (*β* = 0.20) and two-tailed testing (at a type-1 error rate of 5%) is sufficient. Based on the pre-trial with 20 patients (Corr among rep measures = 0.602), a sample size of 12 was targeted as being sufficient to achieve the required effective sample size, but to meet the Chinese Food and Drug Administration standard for the safety and feasibility of nursing staff implementing this inhalation analgesic, the targeted sample size of 120 was recommended.

### Data management and analysis

Data are treated confidentially. To improve the quality of data collection, all researchers will receive professional training before the study. All study-related information (e.g., data collection forms/digital files) will be stored securely in the medical office. Personally identifiable information of participants, such as names, and gender, will be replaced by codes throughout the study and will always remain confidential, with only the project manager or relevant doctors aware of the patient’s personal information.

And any public reports on the results of this study will not reveal any identifiable information about the patient. Composition of data monitoring committee (DMC) and auditing system will be established shortly after the project launch to monitor the collection and management of data and patient safety throughout the study. Members will include four professional therapists and nurses, two pain management specialists, and a senior academic statistician who worked as the board’s chair.

A double data check has also been performed for quality control. According to the data collection methods and criteria developed by the project leader and professionals, all data will be recorded carefully and comprehensively to ensure the authenticity of the data. Missing data on withdrawn participants will be imputed using the multiple imputation method.

All statistical analyses will be performed by SPSS version 25 (IBM Inc, Armonk, New York), with an alpha set at 0.05. Statisticians will calculate the mean (standard deviation), median (interquartile range), minimum, maximum, and proportion (95% confidence interval) for quantitative data and describe numbers and percentages for qualitative data. The mean will be compared by Student’s *t*-test (normal distribution parameter) or nonparametric two-sample Mann–Whitney test (nonnormal distribution parameter). The proportions will be compared using the chi-square test or Fisher exact test. The comparisons between two groups will be performed as follows: *t*-tests or Wilcoxon rank sum (normal or nonnormal ability distributions) for quantitative data; chi-square test or Fisher’s exact test for qualitative data. The value of *P* < 0.05 will be considered statistically significant.

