### Participants

All patients who received MT after ACL reconstruction facing acute pain will be invited to participate in this study. To decrease confounding factors that may interfere with pain scores during the rehabilitation, we will recruit patients with relatively consistent surgical site as much as possible (unilateral joint). The inclusion criteria are as follows: willing to participate in the trial and sign informed consent; man or woman; age ≥ 18 years old; patients underwent primary unilateral ACL reconstruction (1 month post-operative, with or without meniscal injury or collateral injury); experience worst pain (during MT) was reported ≥ 4 (on a visual analogue scale (VAS) of 0–10 cm); without postoperative complication. Exclusion criteria include the following: patients with pain unrelated to MT; patients who have undergone other surgical operations on the knee except for ACL; mental disorder or altered mental status have difficulty in reporting pain; patients with contraindications to N_2_O (abdominal distension or suspected bowel obstruction, air embolism, pneumothorax, decompression sickness, epilepsy, pulmonary cancer, chronic obstructive pulmonary disease and acute respiratory infection, pregnancy, severe inhalation injury, pharmaceutical or pathological pulmonary fibrosis, maxillofacial injuries, disease involving ear, nose, larynx, such as sinuses, otitis media); drug dependence or abuse. The main inclusion and exclusion criteria are presented in Table 2.

**Table 2 Tab2:** Main inclusion and exclusion criteria

**Inclusion criteria**	**Exclusion criteria**
Patients with acute pain caused by manual treatment after anterior ligament reconstruction	Patients with mental disorder or altered mental status have difficulty in reporting pain
Age ≥ 18 years old	Patients who have undergone other surgical operations on the knee except for ACL
Willing to participate in the trial and sign informed consent	Drug dependence or abuse
Background worst pain (during Manual therapy) reported being 4 or higher (on a visual analogue scale (VAS) of 0 to 10 cm)	Contraindications to N_2_O (suspected bowel obstruction, air embolism, pneumothorax, epilepsy, chronic obstructive pulmonary disease, and acute respiratory infection, pregnancy, pharmaceutical or pathological pulmonary fibrosis, maxillofacial injuries, disease involving ear, nose, larynx)
Without postoperative complication	

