### Outcome measures

#### Baseline data

The demographic data of all participants (gender, age, height, weight, country, nationality and occupation, etc.) and clinical characteristics (including type and location of damage, current pain level) will be recorded with an internally designed form at baseline (T0, 2 min before the intervention). Vital signs such as blood pressure (BP), heart rate (HR), and oxygen saturation (SPO_2_) will also be collected at baseline.

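### The stated comparison of VAS pain is an unadjusted t-test or rank test chosen by the observed distribution, so the T0 score already collected is not used for adjustment and the primary test is not fixed in advance

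*Protocol article*

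**What the plan says.** **Analysis.** The Data management and analysis section of the protocol article gives one between-group rule for all quantitative outcomes: t-tests "or Wilcoxon rank sum (normal or nonnormal ability distributions) for quantitative data". The same section says, in a separate sentence, that means are compared by Student's t-test or, if the distribution is not normal, by the Mann-Whitney test. It names no covariate, change score or repeated-measures model, and no rule for judging normality. It also plans multiple imputation for withdrawn participants.

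**Baseline.** The Primary outcome section lists VAS at T0, T1 and T2. Table 1 schedules a pain score at all three times. The Baseline data section confirms the T0 record: "current pain level) will be recorded with an internally designed form at baseline". Table 2 adds an eligibility threshold on a different score: "Background worst pain (during Manual therapy) reported being 4 or higher".

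**Sample size.** The calculation is described as "Based on the pre-trial with 20 patients (Corr among rep measures = 0.602"), with the result that "a sample size of 12 was targeted as being sufficient to achieve the required effective sample size". For a safety and feasibility standard, "the targeted sample size of 120 was recommended" instead. The same section calls the primary endpoint the level of pain relief, without defining it.

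**The concern.** The sample size section uses a within-patient correlation. A two-sample t-test or rank test on a single post-baseline value has no such parameter. So the trial is sized with information that the stated comparison leaves out, although the T0 score is available for every patient who completes the schedule.

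Two things are at stake.

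- **Precision.** If T0 pain predicts later pain, leaving it out gives a wider confidence interval than these patients could provide.
- **Pre-specification.** The t-test compares means. The rank-sum test does not, although the text presents it as an alternative way to compare the mean. Nothing says whether normality is judged by arm, by time point or by which criterion. VAS is bounded at 0 and 10, so the non-normal branch could well be taken. The hypothesis tested for the primary outcome, and whether a mean difference accompanies it, would then be settled after the data are seen. A rank-sum P value alone also gives no estimate and standard error to combine across imputed data sets.

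**Working it through.** **Inputs**

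- From the Sample size estimates section: two-sided alpha 0.05, power 80%, correlation 0.602 from 20 pilot patients, N = 12 from the calculation, N = 120 planned.
- From the Study design section: 1:1 allocation, hence 60 per arm.
- Not stated: effect size, SD, and which pair of time points the 0.602 describes. Standardised differences below are therefore assumptions.

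**Step 1. The plan's own figure.** N = 12 cannot be reproduced, because no effect size is given. It can only be solved backwards. For 80% power with 12 patients and correlation 0.602:

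- within-patient or interaction test, 3 measurements: f about 0.352 (12 remains the answer up to just under 0.394)
- within-patient or interaction test, 2 measurements: f about 0.40
- between-group test, 3 measurements: f about 0.77
- plain t-test, 6 per arm: d about 1.80

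At d = 1.80, an unadjusted t-test with 60 per arm has power above 99.9%.

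**Step 2. Variance of the treatment difference, relative to an unadjusted comparison of post-values.** Let r be the T0-to-post correlation, with equal SDs at both times.

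- ANCOVA on T0: 1 − r² = 1 − 0.602² = 1 − 0.362 = 0.638, a saving of 36%.
- Change from T0: 2(1 − r) = 2 × 0.398 = 0.796.
- ANCOVA against change: 0.638 / 0.796 = 0.801, a saving of 20%.
- Equivalent sample size: 120 / 0.638 = about 188 patients analysed without adjustment.

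**Step 3. Power at 60 per arm, r = 0.602.**

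- Difference detectable with 80% power, unadjusted: 0.516 SD (noncentral t).
- With ANCOVA: 0.516 × √0.638 = 0.412 SD.
- Power at 0.516 SD: 80% unadjusted, 94% with ANCOVA (noncentral t, 117 degrees of freedom). A simulation of 4,000 trials gave 80.1% and 93.2%.

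**Step 4. Sensitivity to r.**

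| r | Saving against raw post-values, r² | Equivalent N, 120/(1 − r²) | Saving against change, (1 − r)/2 |
|---|---|---|---|
| 0.3 | 9% | 132 | 35% |
| 0.4 | 16% | 143 | 30% |
| 0.5 | 25% | 160 | 25% |
| 0.602 | 36% | 188 | 20% |
| 0.7 | 49% | 235 | 15% |

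If 0.602 is treated as a single correlation from 20 patients, Fisher's transformation gives an approximate 95% interval: arctanh(0.602) ± 1.96/√17, back-transformed, is 0.22 to 0.82. The saving against raw post-values then runs from 0.22² = 5% to 0.82² = 68% (unrounded limits 0.217 and 0.825).

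**The case against.** The strongest reply is that nothing here endangers the trial's conclusion, and that largely stands. In a 1:1 randomised trial the unadjusted t-test controls the type I error, and its standard error already allows for chance imbalance at T0. A reader might infer that the trial is underpowered. The documents do not support this: 12 patients were said to suffice, 120 were chosen for another reason, and the benchmark of 0.516 SD is derived here and is not a stated target.

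A reader might also infer that a third of the variance is certainly wasted. That goes too far. The 0.602 is one pilot figure and is not said to be a T0-to-T1 correlation. T0 precedes manual therapy, whereas the pain of interest arises during it, so the relevant correlation may be lower. If the level of pain relief means change from T0, then T0 is used in part and the remaining saving is about 20%. The Primary outcome section, however, defines the outcome as the degree of pain, and the analysis section mentions no change score.

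Three further limits hold.

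- The worst-pain score appears only as an eligibility threshold and is not in the Table 1 schedule. It cannot be assumed to be available as a covariate.
- A rank analysis can be given an estimate with an interval (for example a Hodges-Lehmann shift), and such an estimate could be pooled. The difficulty is with the bare P value, which is all that the text provides for. With 60 per arm the two tests will usually agree.
- Choosing T1 as the only primary time point would be a separate change.

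An unseen analysis plan might add detail. That does not answer the point, because the article does not leave the test open: it states unadjusted tests and a distribution-based choice between them.

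**Conclusion.** The point holds as an improvement that costs nothing, not as a defect that invalidates the analysis. The article states an unadjusted comparison with a test chosen by the observed distribution, while collecting T0 VAS and sizing the trial with a repeated-measures correlation.

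The size depends on two unknowns. If raw post-values are compared and the T0-to-post correlation is 0.602, the variance given up is about 36%. If change scores are compared, it is about 20%. Both figures assume equal SDs at T0 and afterwards and a linear relation. Correlations of 0.3 to 0.7 give 9% to 49% against raw post-values, and the pilot is too small to narrow that range.

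The pre-specification part does not depend on the correlation: as written, the data decide which hypothesis is tested for the primary outcome.

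**What to change.** Before unblinding, state in the analysis plan that:

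1. VAS at the primary post-baseline time point or points is analysed by a linear model on treatment group and T0 VAS: ANCOVA for a single time point, or a mixed model with T0 as covariate if T1 and T2 are analysed together.
2. The result is the adjusted mean difference with 95% CI, pooled across the planned imputations.
3. The distribution-based choice of test no longer applies to VAS, and a rank test is reported as a sensitivity analysis.
4. The screening worst-pain VAS is added as a covariate only if its value was recorded for every patient.

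The cost is a paragraph of text and a few lines of SPSS syntax, with no new patients or measurements. The Trial status section reports 98 of 120 participants included, and the cylinders stay labelled A and B until trial procedures are complete. If the allocation is still concealed, the change can be made and dated without knowledge of the results. Once the code is broken, that could no longer be shown.

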### Safety and AE monitoring

Side effects include dizziness, headache, nausea, vomiting, lethargy, euphoria, oxygen destruction (pulse oxidative saturation ≤ 94%), arterial hypotension, bradycardia, or any other uncomfortable reactions that will be assessed and recorded during and after the procedure. In case of any of the above conditions, the inhalation of gas will be stopped immediately and oxygen will be given to the patient, then the discomfort will rapidly disappear within 5 min [28, 29].

### Quality control

The research will be coordinated and supervised by pain management specialists, rehabilitation therapists, nurses, and senior statisticians. To ensure the quality of the study, at the beginning of this study, the project manager and team members formulated a detailed project protocol and emergency plan. During the trial, researchers will receive unified and targeted training to ensure the smooth implementation of the study. The study funders will use the audits to regularly check the source of the data and its accuracy, integrity, reliability, and security.

## Discussion

From an orthopedic perspective, postoperative rehabilitation plays an important role in maximizing the patients’ functionality and helping the management of these potential post-operative problems [30]. However, MT is conducted when the patient is conscious. Pain may be a major obstacle to MT sessions in this population [31, 32]. Proper pain management and timely ROM acquisition after surgery can not only improve patients’ satisfaction and quality of life but also reduce the burden on nursing staff and the economic burden of the patient group on health and social care services.

Our unpublished preliminary qualitative interview indicated that patients were asked to endure severe pain but no analgesics were supplied. The reasons for poor pain management may include medical workers’ and patients’ resistance to opioids, inappropriate cognitive understanding of pain, and lack of systematic pain management education [33–35].

The appropriate analgesics are integral for pain control postoperative of ligament reconstruction. Compared with traditional opioid analgesics, N_2_O is a self-administered inhaled gas reserved in a pre-prepared cylinder and has the characteristics of analgesia, sedation, and anti-anxiety. It has been widely used for nearly a century in other countries, especially in Britain, Sweden, the Netherlands, and Australia. The use rate of nitrous oxide is as high as 80% [36], which is mainly used in clinical disciplines such as dentistry, emergency, obstetrics and gynecology, pediatrics, and postoperative analgesia. It is reported that the mixture of 20% N_2_O and 80% O_2_ has an equivalent analgesic effect as well as a good sedative effect with 15 mg morphine [37]. Notably, it does not combine with hemoglobin and is mainly discharged through the lungs with a strong analgesic effect but a weak anesthetic effect [31, 38].

Therefore, we designed this study to explore the efficiency of N_2_O for patients receiving MT after ACL reconstruction. If feasible, it will be widely applied in rehabilitation training after ACL reconstruction and improve the quality of life and satisfaction of patients.

## Limitation

Some limitations must be acknowledged in this study. Firstly, the pain score was the subjective outcome and was not consistently assessed by individual patients; therefore, it is susceptible to the subjective influence of patients. Secondly, data extraction is only during and after the procedure, without long-term effect records.

## Conclusion

To our best knowledge, this study is the first randomized controlled trial to evaluate the effectiveness of the N_2_O to treat acute pain in patients undergoing MT after ACL reconstruction. If this treatment appears beneficial, this study can help to generate preliminary guidelines on pain management in patients undergoing MT. We will disseminate the results of this study to international journals and conferences.

## Trial status

This trial has been registered in the clinical trial registry: ChiCTR2200061175 (Version 2.0 June 15, 2022). Participant recruitment began on June 27, 2022, and is expected to be completed within 1 year. At the time of writing the manuscript, a total of 98 participants had been included in the study. The participating clinical centers are positively recruiting and collecting data.

## Data Availability

After the completion of the study, the final trial data and statistical code will be obtained from the project leader for reasonable reasons. No project member can get the data privately.

## Abbreviations

ACL: Anterior cruciate ligament
MT: Manual therapy
N_2_O: Nitrous oxide
O_2_: Oxygen
HR: Heart rate
BP: Blood pressure
SPO_2_: Oxygen saturation
VAS: Visual analogue scale
ROM: Joint range of motion
